**Fig. 3 Fig3:**
[figure not shown]
Assessments and intervention timeline. Wk, week; M., month; FFQ, food frequency questionnaire; RMR, resting metabolic rate; WOMAC, the Western Ontario and McMaster questionnaire; IPAQ, International Physical Activity Questionnaire; DASS-21, Depression Anxiety Stress Scale questionnaire; HRQoL, Health-Related Quality of Life

#### Day 1

On the first day of the study, participants will attend the laboratory in a fasting condition between 8 and 9 am.

##### General information collection

All data and tests will be collected by sport scientists, with the exception of the food frequency questionnaire, which will be performed by a nutritionist, the exercise testing, which will be performed by a sports and exercise physician, and the collection of blood and stool samples, which will be performed by a nurse. The data collection process will include the following variables: sex, date of birth, mode of transportation to the research center (car, walking, or public transport), level of education, and dominant hand (left or right).

##### Resting metabolic rate (RMR)

RMR will be assessed with a canopy utilizing the Cosmed Quark (Cosmed, Rome, Italy). Participants will lie on a gurney in the supine position for 30 min while wearing a canopy. The data collected during this time will be processed with the Omnia computer software provided by Cosmed. The data collected will include RMR (kcal/day), respiratory quotient, oxygen consumption (VO_2_; ml/min), production of carbon dioxide (VCO_2_; ml/min), and energy obtained from lipids, carbohydrates, and proteins.

##### Anthropometric data

Height and sitting height will be measured without shoes with a stadiometer SECA 225 (SECA, Hamburg, Germany) to the nearest 0.1 cm. Body mass (kg) and body composition (fat and fat-free mass) will be collected with a bioimpedance device (TANITA MC780MA-N, Tanita, Tokyo, Japan).

##### Body composition

A Hologic Horizon QDR dual energy X-ray absorptiometry (DXA) scanner (Hologic Inc, Bedford, MA) will be used to perform whole-body, hip, and lumbar spine scans. The left hip will be measured in all participants. The three scans will yield areal BMD (aBMD, g/cm^2^), bone mineral content (BMC, g), and bone area (cm^2^). The Horizon QDR series enables for a whole-body scan in patients with morbid obesity as the arm and/or leg can be placed outside the scanning area (due to the size limitations of the DXA device, it may not be possible to scan the entire body of large patients). The software will then copy the complete scanned arm or leg to the arm or leg with missing information. In addition to the assessment of aBMD, BMC, and bone area, the whole-body scan will also yield data on lean and fat mass (in grams) and visceral adipose tissue (area in cm^2^, volume in cm^3^, and mass in grams) from the whole-body scan. The trabecular bone score will also be determined using the Hologic-specific software (TBS Hologic).

The bone structure, strength indexes, and BMC of the non-dominant forearm will be measured using a peripheral quantitative computed tomography (pQCT) using a Stratec XCT-2000 L pQCT scanner (Stratec Medizintechnik, Pforzheim, Germany). The forearm will be measured at 4% of the total length to evaluate trabecular bone and at 66% of the total length to evaluate cortical bone. The coefficients of variation for the pQCT in our laboratory have been published elsewhere [39].

Although the International Society of Clinical Densitometry recommends bone scans to be performed with a year difference when a new treatment has begun (in our case the exercise treatment), they also state that in conditions associated with rapid bone loss, testing more frequently is appropriate [40]. It has been demonstrated that BS has a detrimental effect on bone loss, particularly in the initial year following surgery [16]. Previous studies have indicated that significant bone loss can occur as early as 6 months post-surgery [41].

##### The Western Ontario and McMaster (WOMAC) questionnaire, International Physical Activity Questionnaire (IPAQ), and Depression Anxiety Stress Scale questionnaire (DASS-21)

The three questionnaires will be completed by the participants with the assistance of the researchers in an interview format. The WOMAC questionnaire [42] will be used to ascertain the degree of knee and hip pain experienced by the participants. The short version of IPAQ will be used to determine the levels of physical activity and sitting time. The DASS-21 questionnaire will be employed to evaluate depression, anxiety, and stress in the Spanish version [43].

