### Intervention

#### Randomization, allocation, and blinding

In order to ensure fairness, individuals who meet the eligibility criteria will be randomly assigned (1:1) to either a WBV group or a CG through the webpage https://www.sealedenvelope.com, taking sex into account (1:1). At the second visit, both groups will be provided with a brochure outlining the World Health Organization’s physical activity recommendations, as well as an ad hoc nutritional information sheet. A nurse will be responsible for recruiting all participants and will then direct them to the researchers, who will inform the participants of their group allocation, in accordance with the randomized order. Both groups will receive standard care, but the intervention group will also engage in an exercise intervention as outlined below. Given that the intervention will comprise WBV and that researchers will be involved in it, only the nurse and the statistician performing the statistics will be blinded. There is no foreseeable reason for the statistician to be unblinded to participant allocation.

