#### Intervention description

##### Supervision and adherence

All training sessions will be overseen by a sports scientist with prior experience in working with WBV platforms. The training will be conducted on a one-to-one basis, with the trainer guiding the participant through each session.

The trainer will contact participants each week via WhatsApp to schedule the upcoming training sessions. The training will be provided free of charge for all participants and will be conducted at the GENUD-Lab (University of Zaragoza, Spain), with no home-based component. The laboratory is equipped with a dedicated space for WBV training and a Smith machine, which will be employed for the attachment of elastic bands and the development of the elastic band training.

During each training session, the trainer will record the following information in each participant’s training book:Date and the participant’s attendance at the training sessionWarm-up: Cycling Watts, perceived exertion (using a validated OMNI scale specific for cycle ergometer [33]) and heart rate (using a Polar H10 heart rate sensor)WBV training: heart rate and perceived exertion (using a validated visual scale [34] specific for WBV) at the midpoint and conclusion of the training sessionElastic band training: the color of the elastic band, heart rate, and perceived exertion (using a validated visual scale specific for Thera-Band bands [35])Adverse effects during the session (pain, discomfort, etc.)Exercises performed by the individual during the previous 72 h outside of the laboratory

At the conclusion of each month, the trainer will evaluate the participant’s attendance percentage and offer constructive feedback to those with a high attendance rate. For those with a low attendance rate, the trainer will discuss potential causes and solutions to improve attendance. In order to progress to the subsequent week, a minimum of two sessions of assistance is required. For instance, should a participant complete only one session in week 5, the following week they will perform one session of week 5 and two sessions of week 6, rather than three sessions of week 6. This adaptation ensures that the increase in intensity is gradual and therefore more manageable. There are no other criteria for discontinuing or modifying allocated interventions. Participants may withdraw voluntary from the trial at any point. They may provide no reason for their withdrawal or may provide any reason they see fit.

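### Three secondary questionnaires (WOMAC, IPAQ short form, DASS-21) are taken by interview with unblinded researchers from the team that delivers the WBV training, which lets interviewer influence differ by arm

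*Protocol article*

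**What the plan says.** Four statements in the protocol article bear on this.

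- Mode (section on WOMAC, IPAQ and DASS-21): "The three questionnaires will be completed by the participants with the assistance of the researchers in an interview format". WOMAC covers knee and hip pain, the short IPAQ covers physical activity and sitting time, and DASS-21 covers depression, anxiety and stress.
- Blinding (Randomization, allocation, and blinding): "Given that the intervention will comprise WBV and that researchers will be involved in it", the article continues, "only the nurse and the statistician performing the statistics will be blinded". The same section says that the recruiting nurse "will then direct them to the researchers, who will inform the participants of their group allocation".
- Data collection (General information collection): "All data and tests will be collected by sport scientists, with the exception of the food frequency questionnaire". The other exceptions are the exercise test and the blood and stool samples. None covers these three questionnaires.
- Training (Supervision and adherence): "All training sessions will be overseen by a sports scientist with prior experience in working with WBV platforms", one-to-one with the participant.

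Training and testing both take place in the GENUD-Lab. Under Outcome variables, the three questionnaires are not among the four primary outcomes, so they are secondary. The Accelerometer section adds a 7-day device record of physical activity, sedentary time and sleep.

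**The concern.** Participants cannot be blinded to an exercise programme. Whether an unblinded researcher takes part in each answer is, however, a matter of choice. Here that researcher knows the allocation and belongs to the group that delivers the training and that, in the abstract, states that it expects the WBV arm to improve more.

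Contact with the team is also very unequal. A WBV participant may have up to 47 supervised sessions, weekly scheduling messages and monthly attendance feedback. A control participant receives standard care with no matched contact.

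If the interview setting changes what people report, it can do so differently in the two arms. Such a difference arises after allocation, so the baseline measurement does not remove it. It would be read as part of the group-by-time interaction, which is the planned test. At stake is whether differences in reported pain, mood and activity can be attributed to the training.

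**Working it through.** **1. The text, set side by side.**
- The interviewers for these instruments are researchers, by the questionnaire section.
- Researchers are not blinded, by the blinding section, and the reason given is their part in the intervention.
- Data collectors and trainers are both described as sport(s) scientists.
- So the interviewers are unblinded and come from the team that delivers WBV. The article does not say that one individual both trains and interviews the same participant.

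**2. When it could act.** T2 is at 7 ± 1 weeks and T3 at 24 ± 2 weeks after surgery (Study design). Assuming that the 16-week programme follows T2, it ends near week 7 + 16 = 23, just before T3. Familiarity with the team would therefore differ most between arms at T3. T4, at 18 months, comes about a year later.

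**3. Which outcomes have a check.** Physical activity and sedentary time are also measured by accelerometer, a partial check on IPAQ. Pain, depression, anxiety and stress have no objective counterpart.

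**4. The group size used below.** The article plans 12 per group before attrition, from partial eta squared 0.06, correlation 0.5, two groups and four measurements.
- f² = 0.06 / 0.94 = 0.0638
- λ = N × f² × m / (1 − ρ) = 24 × 0.0638 × 4 / 0.5 = 12.26, with 3 and 66 degrees of freedom
- Power is 0.825 at N = 24 and 0.784 at N = 22, so the stated 24 reproduces. It serves here only as the group size.

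**5. Illustration of what a shift would do.** The documents give no size for such a bias, so a shift b (in SD units, one arm only, no true effect) is assumed. The test is a two-sided two-sample t-test at 5%.
- Standard error with 12 per arm: √(2/12) = 0.408 SD
- Noncentrality: δ = b / 0.408
- Error rate: probability that a noncentral t on 22 degrees of freedom with this δ exceeds the critical value in either direction

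| Assumed shift b | δ (12 per arm) | Error rate, 12 per arm | Error rate, 14 per arm |
|---|---|---|---|
| 0.2 SD | 0.49 | 7.6% | 8.0% |
| 0.3 SD | 0.73 | 10.8% | 11.9% |
| 0.5 SD | 1.22 | 21.6% | 24.7% |

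This is one comparison at one time point, not the planned repeated-measures ANOVA over four assessments. It shows how sensitive a trial of this size is to such a shift; it does not estimate the bias in this trial.

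**The case against.** The strongest reply is that the article openly discloses its limited blinding and the reason for it, that only secondary outcomes are touched, and that one interview format for both arms is a legitimate way to limit missing or misunderstood items when there are only 24 to 28 participants. All of that stands. It limits the weight of the point, but it does not explain why researchers involved in the training should conduct these interviews.

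A reader might also infer more than the documents support:

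- **That the trainer is the interviewer.** No statement says so. Staffing at that level is commonly left to the full protocol. The text supports only unblinded interviewers from the same team.
- **That primary quality of life is affected.** The section on EQ-5D-5L and SF-36 states no interview format, and the interview statement refers to the other three questionnaires. An unstated mode in a condensed article is no basis for a finding.
- **That the bias favours WBV.** This is plausible, but not established. The trainer records pain and discomfort at each session and asks about exercise outside the laboratory over the previous 72 h. Familiarity could equally increase disclosure of symptoms or make activity reports more accurate.
- **That the bias can be removed, or can never be separated from a true effect.** Participants know their arm whoever asks, so self-completion removes the interviewer's part and not expectation. For activity, the accelerometer offers some separation.
- **That 11% to 22% measures what the fix would recover.** Those rates rest on an assumed shift credited wholly to interview mode, although part of any shift would persist under self-completion.

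**Conclusion.** The point holds as a limited one about three secondary questionnaires. The stated procedure exposes reported pain, activity and mood to interviewer influence that can differ by arm after allocation, most plausibly at T3, and part of that exposure is avoidable at low cost. It matters most for pain, depression, anxiety and stress, and less for activity.

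The size and direction of the bias cannot be derived from the documents. The error rates of about 11% and 22% depend on an assumed shift of 0.3 or 0.5 SD, 12 per arm, no true effect and a single two-sample comparison. The judgement about T3 assumes that training follows T2. Nothing here shows that bias will occur, or that the primary outcomes are affected.

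**What to change.** In the section on WOMAC, IPAQ and DASS-21, replace the assisted interview with self-completion:

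- Participants fill in the three questionnaires themselves, on paper or tablet, at the start of the visit.
- Help is limited to reading items aloud or clarifying wording and, where existing staffing allows, is given by someone who has not trained that participant.
- The same mode is used at T1 to T4.
- For anyone already interviewed, the mode used at each assessment is recorded.

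The cost is printed or tablet forms and a short change of text. Self-completion itself needs no extra staff. The article gives no staff numbers, so the condition on who helps is a preference and not an absolute rule. The downside is a few more missing or unclear items, limited by a completeness check at hand-in. Reports of results should still acknowledge that participants knew their allocation.

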##### Dietary intake

A semiquantitative food frequency questionnaire [44] will be completed at the initial, third, and fourth assessments. The questionnaire comprises 133 items divided into nine food groups: (1) dairy products (15 items); (2) eggs, meat, and fish or seafood (23 items); (3) vegetables (18 items); (4) fruits (16 items); (5) legumes and cereals (11 items); (6) oils and fats (11 items); (7) pastries, cakes, or sweets (13 items); (8) a miscellaneous group (12 items); and (9) drinks (14 items). The questionnaire will refer to the preceding year and will be completed through an interview with a nutritionist. Each item included is accompanied by a description of the typical portion size. The participants will select the frequency of consumption between nine options (ranging from never to six or more times per day). Nutrient intake scores will be calculated using an ad hoc computer program designed for this purpose [45]. This will involve multiplying the frequency of consumption by the nutrient composition of a specified portion size. The selected frequency item will be converted to a daily intake. For example, if a response is 5–6 times a week, it will be converted to 0.78 servings per day. Portion size will be multiplied by the frequency of consumption in order to obtain the daily intake. The data extracted from this questionnaire will comprise total mean energy intake (kcal/day), macronutrients (protein, fat, and carbohydrates in g/day and % kcal of the total macronutrient energy distribution), alcohol (g and % kcal of the total macronutrient energy distribution), types of fatty acids (g/day), types of polyunsaturated fatty acids (PUFA) (n-3 and n-6) (g/day), and vitamins and minerals (mg or µg/day as corresponding to the nutrient in question).

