## Material and methods

### Study design, research ethics approval, protocol registration, and reporting

This protocol is a two-arm superiority randomized controlled trial. It has been registered in Clinicaltrials.gov NCT05695599 and approved by the Ethics Committee of Clinical Research of Aragón (CEICA, Spain) with reference number C.I. PI22/380. In the event that changes to the protocol are necessary during its implementation, permission will be sought from the Ethics Committee before applying the changes. Participants will be randomly assigned to one of two groups: (1) the control group (CG) or (2) the WBV group. The study design and this protocol manuscript adhere to the SPIRIT reporting guidelines and the SPIRIT 2013 checklist is presented in Supplementary Table 1 [27]. Moreover, the exercise intervention is explained in accordance with the Consensus on Exercise Reporting Template (CERT): Explanation and Elaboration Statement [28]. The 16 items that should be completed in accordance with the CERT are presented in Supplementary Table 2.

As illustrated in Fig. 1, the study will span a period of 18 months. Four different assessments will be conducted at various intervals: T1 (approximately 1 week before the surgery), T2 (7 ± 1 weeks post-surgery), T3 (24 ± 2 weeks post-surgery), and T4 (18 months ± 2 weeks post-surgery).

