##### Training frequency, intensity, and duration

Those allocated to the WBV group will attend three weekly supervised sessions for 16 weeks, with a total of 47 sessions completed (during the first week, only two sessions are performed). Participants will be permitted to select the time of day and day of the week for each session, provided that a minimum of 24 h elapsed between each session and that the training is not performed on three consecutive days.

The duration of the sessions will range from 28 to 46 min, with the intensity increasing weekly through an increase in the number of repetitions, time of vibration, or reduction in rest times as illustrated in Table 1.

In the WBV, all participants will receive the same stimulus, resulting in varying internal loads for each individual. Nevertheless, for the warm-up and the elastic band training, the resistances will be adjusted as previously explained in order to achieve a similar internal load for all participants.

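### The one-year food-frequency recall at the 24-week visit reaches back before surgery for about half its length, so T3 intake blends pre- and post-surgical diet and understates change

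*Protocol article*

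**What the plan says.** The Dietary intake section of the protocol article says that the food-frequency questionnaire "will be completed at the initial, third, and fourth assessments", and then sets the recall period: "The questionnaire will refer to the preceding year and will be completed through an interview with a nutritionist". The rule is stated once, with no exception for any visit.

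The visit times are in the section on study design, ethics approval, registration and reporting: "T1 (approximately 1 week before the surgery"), "T2 (7 ± 1 weeks post-surgery") and "T3 (24 ± 2 weeks post-surgery), and T4 (18 months ± 2 weeks post-surgery"). Under Training frequency, intensity, and duration, the vibration group "will attend three weekly supervised sessions for 16 weeks".

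Diet is not named among the primary outcomes, so under Outcome variables it is secondary. The article describes no other dietary measure, such as a food diary.

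**The concern.** Surgery falls inside the T3 recall window. A participant following the rule must give one average frequency per food item across two different eating periods, one before and one after sleeve gastrectomy. The T1 to T3 contrast then compares a pre-operative year with a year that is roughly half the same pre-operative time.

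Two uses of the data are at stake:

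- **Diet as a secondary outcome.** Change from baseline and any difference between arms at T3 are both pulled towards zero.
- **Diet as an explanatory variable.** Stool is collected at the same three assessments, in tubes meant to capture the microbiota at one moment. The Background says that microbiota changes after bariatric surgery overlap with those due to altered food habits, and Statistical methods plans correlations and regressions between variables. Any of these that uses T3 diet would set a current measurement beside an average that is about half pre-operative.

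**Working it through.** The article gives no figure for the share of the recall window before surgery, so there is none to reproduce. The check sets the stated recall period against the stated visit times.

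**Inputs**

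- Recall window: one year, taken as 52 weeks (Dietary intake).
- T1: about 1 week before surgery. T2: 6 to 8 weeks after. T3: 22 to 26 weeks after, nominally 24. T4: 18 months ± 2 weeks after (study design section).
- Training: 16 weeks. Its start is assumed to be about T2, because the timeline figure is not shown.

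**1. Pre-operative share of the T3 window** = (52 − weeks since surgery) / 52

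- Week 22: 30/52 = 57.7%
- Week 24: 28/52 = 53.8%
- Week 26: 26/52 = 50.0%

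**2. Overlap with the T1 window.** At the nominal visit the T3 window runs from 28 weeks before surgery to 24 weeks after. The T1 window ends 1 week before surgery. The overlap is 28 − 1 = 27 weeks, or 27/52 = 52% of the T3 window.

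**3. Attenuation of a change present since surgery.** Let P be the pre-operative level and Q a constant post-operative level, with every week weighted equally. At week 24 the T3 reading is (28P + 24Q)/52, and T1 reads P. The observed change is (24/52)(Q − P), or 46% of the true change. Over the visit window this is 22/52 = 42% to 26/52 = 50%.

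**4. Attenuation of an arm difference confined to training** = training weeks inside the window / 52

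- All 16 weeks inside the window: 16/52 = 30.8%
- Least favourable timing (T2 at week 8, T3 at week 22): 14/52 = 26.9%

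**5. Does another administration cover the training period?**

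- T1 is wholly pre-operative.
- T2 has no questionnaire.
- T3 is mixed, as above.
- T4: 18 months is 78.3 weeks and a year is 52.2 weeks, so the window opens at 78.3 − 52.2 = 26.1 weeks after surgery, or 24.1 to 28.1 with the ± 2 weeks. Training that starts at weeks 6 to 8 ends at weeks 22 to 24, so the T4 window opens after training has finished.

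No administration isolates diet during training.

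**The case against.** The strongest reply is that this is a minor matter on a minor variable. Diet is absent from the listed Objectives, the exercise rationale and the Conclusions claim no training effect on it, and no diet-adjusted model is named for microbiota or body composition. That stands, and it limits the weight of the point.

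The percentages are also calendar shares, not measured bias. They become attenuation factors only if respondents average evenly over the year and the post-operative diet is roughly constant; the 31% further requires an arm difference that exists only during training. Respondents who lean towards recent eating would show less attenuation. This stands too, but it does not rescue the rule. If some participants report current diet and others the whole year, the effective window varies by person, which is hard to absorb with 14 per arm.

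It may be said that the questionnaire is by design a one-year instrument, or that an interviewer manual not shown here anchors T3 differently. The first explains the wording without removing the conflict with a 24-week visit. The second is possible, but the article states the one-year rule explicitly and without exception.

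Two stronger readings are tempting and are not supported:

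- A reader might infer that T3 intake cannot show post-surgical diet or a training effect at all. Under even averaging both are attenuated, not erased, and at week 26 the pre-operative share is exactly half, not more than half.
- A reader might infer that the T3 microbiota and body-composition results become uninterpretable. The comparison of randomised arms on those outcomes does not depend on diet adjustment. Only their explanation through T3 diet is weakened.

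**Conclusion.** The recall period and the T3 visit time do not fit together. About half of the T3 window is pre-operative: 54% at week 24, with a range of 50% to 58%. That rests only on the stated visit times and a 52-week year. T3 intake is therefore a blend. Under even averaging it shows about 46% of a change present since surgery and, with training starting at about T2, no more than about 31% of an arm difference confined to training.

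The consequence is limited to T3 diet as a secondary outcome and as an explanatory variable. Primary outcomes, sample size and the randomised comparisons are not touched. The change should still be made, because the post-surgical part cannot be separated out once a T3 interview has been done.

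**What to change.** In the Dietary intake section, give T3 its own reference period, identical in both arms and wholly after surgery. Time since surgery brings the pre-operative share to 0%. Time since the T2 visit is the better choice if diet during training is the target. Keep the same items, portion sizes and frequency categories. Keep the preceding year at T1 and T4, where the window lies wholly before or wholly after surgery. State the differing T3 period wherever diet is reported.

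The cost is modest but is more than a changed interviewer instruction:

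- Recall length will differ between visits, so seasonality may enter the T1 to T3 and T3 to T4 contrasts, and T3 departs from the instrument's usual year.
- The protocol requires Ethics Committee permission before a change is applied.
- If some T3 interviews have already been held (the article does not say), record which recall period each participant was given and do not pool the two without comment.

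If the one-year recall is kept at T3, the report should say that T3 intake mixes pre- and post-operative diet and that change from baseline is attenuated.
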